## Sample size

G*power 3.1 software will be used to calculate the sample size required to detect changes in the primary outcome (NPRS scale and JPSE). The calculations will be based on the detection differences of 2.5 points in the NPRS (MCID (minimal clinically important difference) (estimated for a variance in patients with neck pain of 10 points)^40^, assuming a standard deviation (SD) of 2.5 points.

Assuming an effect size (F-test) of 0.27 for ANOVA: repeated measures, within-between interaction groups differences, an alpha level of .05, and power of 80%, a total sample size of 30 participants will be estimated. The sample will be inflated by 10% to account for potential dropouts, resulting in a final target sample size of 34. This calculation showed that a sample size of 17 participants per group will be needed for a confidence interval of 95%, with a power of 80%, assuming a bilateral significance of .05.

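### The effect size f = 0.27 does not follow from a 2.5-point difference and an SD of 2.5, which give f = 0.25; at the correlation implied by N = 30, the target of 34 holds no dropout allowance

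*Protocol*

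**What the plan says.** The Sample size section of the protocol names the NPRS and JPSE as primary outcome but gives numerical inputs only for the NPRS: "The calculations will be based on the detection differences of 2.5 points in the NPRS", "assuming a standard deviation (SD) of 2.5 points". The same sentence carries a second measure of spread: "estimated for a variance in patients with neck pain of 10 points".

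The next sentence brings in the standardised effect, "Assuming an effect size (F-test) of 0.27 for ANOVA: repeated measures, within-between interaction groups differences", with "an alpha level of .05, and power of 80%, a total sample size of 30 participants will be estimated". Dropout follows: "The sample will be inflated by 10% to account for potential dropouts, resulting in a final target sample size of 34". The paragraph closes by saying that "a sample size of 17 participants per group will be needed" for 80% power, "assuming a bilateral significance of .05".

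The Statistical Analysis section plans a two-way repeated-measures analysis of variance with two groups and two times (baseline and post-treatment). No correlation between the two measurements is given, and the text does not say whether 2.5 is the SD of raw scores or of change.

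**The concern.** The difference, the SD and the standardised effect are offered as one calculation, but the first two do not produce the third. A modest overstatement of f matters here because the dropout allowance is only four pilots. If the correct f needs 34 evaluable pilots, the number presented as inflated is really the uninflated requirement, and the claim of 80% power after 10% loss fails. The closing sentence of the paragraph already treats 17 per group as the number needed for power, so 34 plays both roles. A variance of 10 also cannot stand beside an SD of 2.5, because that SD is a variance of 6.25.

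**Working it through.** **Inputs.** From Sample size: difference 2.5, SD 2.5, f = 0.27, alpha 0.05 two-sided, power 80%, N = 30, dropout 10%, final N = 34. From Statistical Analysis: 2 groups, m = 2 time points. Assumed, because it is not stated: a correlation ρ between baseline and post-treatment.

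**Formula.** For the within-between interaction as G*Power computes it, λ = N f² m / (1 − ρ), with a noncentral F on 1 and N − 2 degrees of freedom. N is searched in steps of 2 to keep the groups equal.

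**1. The plan's own figure.** With f = 0.27 and ρ = 0.5, N = 30 gives λ = 30 × 0.0729 × 2 / 0.5 = 8.75 and power 81.5%; N = 28 gives 78.5%. So 30 reproduces. At ρ = 0.4 the same f needs 36, and at ρ = 0.6 it needs 24, so the stated 30 points to ρ of about 0.5. Dropout: 30 / 0.9 = 33.3, rounded up to 34. The step from 0.27 to 30 to 34 is correct.

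**2. The f that the inputs give.** In a 2 × 2 layout, a 2.5-point difference in change puts each cell's interaction effect at ±2.5/4 = ±0.625. Then f = 0.625 / 2.5 = 0.25. To reach 0.27, the difference would have to be 0.27 × 4 × 2.5 = 2.70, or the SD 2.5 / (4 × 0.27) = 2.31. Neither is stated. A between-group effect at one time point gives f = 0.50, and a variance of 10 gives 2.5 / (4 × 3.162) = 0.198, so these readings do not give 0.27 either.

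**3. Consequence at ρ = 0.5 and f = 0.25.**

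| Evaluable pilots | Power |
|---|---|
| 30 | 75.3% |
| 31 | 76.8% (76.4% if split 14 and 17) |
| 32 | 78.1% |
| 34 | 80.7% |

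The requirement is 34 evaluable. A 10% loss from 34 leaves 34 × 0.9 = 30.6, that is 30 or 31.

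**4. Cross-check with a t-test on change.** At ρ = 0.5 the SD of change is 2.5 × √(2 × 0.5) = 2.5, so d = 1.0. The two-sample noncentral t gives 75.3% with 15 per group and 80.7% with 17 per group, the same as above. If 2.5 is itself the SD of change, d = 1.0 directly and these figures hold whatever ρ is.

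**5. Range if 2.5 is the raw-score SD** (f = 0.25, 30 evaluable).

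| ρ | Power |
|---|---|
| 0.4 | 67.5% |
| 0.5 | 75.3% |
| 0.55 | 79.6% |
| 0.6 | 84.0% |

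Power reaches 80% at ρ of about 0.555.

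**The case against.** The paragraph introduces 0.27 as an assumption. It never says that the figure was computed from 2.5 and 2.5, and it names a second primary outcome that might have supplied it. That stands in part: what can be said is that 0.27 has no shown derivation and does not match the only difference and SD given. It does not remove the conflict, because the paragraph says that its calculations are based on the NPRS difference.

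The correlation of 0.5 is inferred from N = 30. It identifies what was probably entered in the software, not the true correlation. This stands. A reader might infer that power simply is 75%; the documents do not support that without a condition. It holds if 2.5 is the SD of change, or if it is the raw-score SD and the correlation is 0.5. A higher correlation does not rescue the paragraph as written, though: at about 0.56, f = 0.25 reaches 80% with 30 evaluable, but f = 0.27 would then need 26, not the stated 30.

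A reader might also take the variance of 10 literally. At ρ = 0.5 that would mean 54 evaluable pilots, with power of 55% at 30 and 61% at 34. The text does not carry that reading. It contradicts the explicit SD, the figure is given in points and not squared points, and the NPRS runs from 0 to 10, so a slip for the scale range is plausible. It remains a wording conflict to resolve, not evidence of a larger shortfall.

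Finally, the gap is small. It is 2.5 against 2.7 points, and if all 34 finish, power is 80.7%. That is fair, and it limits the size of the point. It does not restore the dropout allowance.

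**Conclusion.** The point holds in a conditional form. The stated difference and SD give f = 0.25, not 0.27, and no reading of them tried here gives 0.27. At the correlation that the stated N of 30 implies (about 0.5), or if 2.5 is the SD of change, 34 is the evaluable requirement. Power after about 10% loss is then roughly 75–77%, some 3 to 5 percentage points below the claim. If 2.5 is a raw-score SD and the correlation is open, power at 30 evaluable lies between about 68% and 84% for correlations of 0.4 to 0.6. The steps from 0.27 to 30 and from 30 to 34 are arithmetically sound; the fault is the link from 2.5 and 2.5 to 0.27. This is a defect in the justification of the sample size. It does not affect the randomisation, the endpoint or the validity of the planned test.

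**What to change.** Restate the Sample size paragraph as follows:

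- Give f = 0.25 for a 2.5-point difference and an SD of 2.5. If 0.27 has another source, state the difference and SD behind it.
- Say whether 2.5 is the SD of raw scores or of change, and which correlation was assumed.
- Report that, under the planned repeated-measures ANOVA, 34 evaluable pilots give about 80% and about 30 evaluable give about 75% (ρ = 0.5, or 2.5 as SD of change), with the range over the correlation if 2.5 is the raw-score SD.
- Reconcile the variance of 10 with the SD of 2.5 (variance 6.25), or reword it if the 0–10 scale range is meant.

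This costs one paragraph and a slightly less favourable power statement. If the sponsor wants to keep 80% after 10% loss under the planned ANOVA and the same assumptions, the target would be 34 / 0.9 = 37.8, that is 38.

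Optionally, and as an explicit change to the Statistical Analysis section, a baseline-adjusted ANCOVA could become the primary comparison. It gives about 86% with 30 evaluable, but only if 2.5 is the raw-score SD and the correlation is 0.5. That figure should not be cited while the ANOVA remains the planned analysis.

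### The effect size f = 0.27 does not follow from the stated 2.5-point difference and SD of 2.5, which give f = 0.25; at the correlation implied by N = 30, power for 2.5 points is about 75–77% after the planned dropout, not 80%

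*Protocol*

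**What the plan says.** All the figures are in the Protocol, Methods, Sample size.

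- Target difference: "The calculations will be based on the detection differences of 2.5 points in the NPRS".
- Variability: "assuming a standard deviation (SD) of 2.5 points".
- Effect size and test: "Assuming an effect size (F-test) of 0.27 for ANOVA: repeated measures, within-between interaction groups differences".
- Error rates and result: "an alpha level of .05, and power of 80%, a total sample size of 30 participants will be estimated".
- Dropout: "The sample will be inflated by 10% to account for potential dropouts, resulting in a final target sample size of 34".
- Closing statement: "This calculation showed that a sample size of 17 participants per group will be needed", again with 80% power and a two-sided 5% level.

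The Statistical Analysis section confirms the layout: two groups, each measured at baseline and after treatment. The Sample size section does not say how 0.27 was obtained and gives no correlation between the two measurements.

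**The concern.** A difference and an SD together fix the effect size for a two-by-two interaction. The section states a difference and an SD, and then an effect size that does not match them. The value entered is slightly too large for the stated difference, so the resulting sample is slightly too small for it.

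The closing sentence hides this. It gives 17 per group as the number needed for 80% power, while the sentence before it reaches the same 34 only after adding participants for dropout. A reader cannot tell whether 34 is the number who must complete or the number to enrol. Someone interpreting a null result would credit the trial with 80% power for 2.5 points after dropout, which the stated inputs do not give at the correlation the protocol's own figure implies.

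**Working it through.** **Inputs from the Protocol.** Difference 2.5 points; SD 2.5; f = 0.27; two-sided alpha 0.05; power 80%; N = 30 before dropout; 10% dropout; 34 enrolled in two equal groups (all from Sample size). Two groups and two time points (Statistical Analysis). **Assumed:** the pre-post correlation ρ, which is not stated.

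**Formula.** For the within-between interaction with m = 2 measurements, the noncentrality is λ = f² × N × m / (1 − ρ), with 1 and N − 2 degrees of freedom.

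**Step 1: reproduce the plan's figure.** With f = 0.27 and ρ = 0.5, λ = 0.27² × 30 × 2 / 0.5 = 8.75 and power is 81.5%. N = 28 gives 78.5%, so 30 is the smallest equal-group total that reaches 80%. Then 30 / 0.9 = 33.3, which becomes 34 in equal groups. Both stated figures reproduce.

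**Step 2: which correlation the plan implies.** Varying ρ in steps of 0.01 with equal groups, f = 0.27 returns N = 30 only at 0.49 to 0.51. At 0.48 it returns 32 and at 0.52 it returns 28. So ρ of about 0.5 comes from the protocol's own result.

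**Step 3: effect size from the stated difference and SD.** In a two-by-two layout each interaction effect is one quarter of the between-group difference in change:

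- f = (2.5 / 4) / 2.5 = 0.25, whatever the correlation.
- Conversely, f = 0.27 means 0.27 × 4 × 2.5 = 2.70 points at SD 2.5, or an SD of (2.5 / 4) / 0.27 = 2.31 at 2.5 points. Neither figure is in the section.
- The section also mentions a variance of 10. Taken as the outcome variance, it gives f = (2.5 / 4) / √10 = 0.20, which is further from 0.27.

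**Step 4: power for the stated difference (f = 0.25, ρ = 0.5).**

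| Evaluable pilots | λ | Power |
|---|---|---|
| 30 | 7.50 | 75.3% |
| 31 | 7.75 | 76.8% |
| 34 | 8.50 | 80.7% |

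Ten per cent of 34 is 3.4, leaving 30 or 31. A two-sample t test at a standardised difference of 1.0 agrees: 15 per group gives 75.3% and 17 per group gives 80.7%. Thirty evaluable pilots have 80% power for about 2.65 points.

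**Step 5: sensitivity to the unstated correlation (f = 0.25, 30 evaluable, SD 2.5 taken as the SD at one time point).**

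| ρ | Power |
|---|---|
| 0.3 | 61% |
| 0.4 | 67% |
| 0.5 | 75% |
| 0.6 | 84% |

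Power reaches 80% with 30 evaluable at ρ of about 0.555. If 2.5 is instead the SD of the change, the result is the same as at ρ = 0.5.

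**The case against.** **The power figures depend on an unstated correlation.** This stands. A reader might infer that the trial has no dropout allowance, or that its power is simply 75%. The document does not support either as an unconditional statement. At a correlation of 0.6, 34 enrolled does carry an allowance for the 2.5-point difference, and on the plan's own terms the step from 30 to 34 is a correct inflation. What the correlation cannot repair is the mismatch between 0.27 and 0.25. Nor can the sponsor adopt a higher correlation and keep N = 30 as the result of f = 0.27, because the two are incompatible.

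**The protocol never says that 0.27 was computed from 2.5 and 2.5.** True: the value is introduced as an assumption, and two primary outcomes are named, NPRS and JPSE. But the section says that the calculations rest on the NPRS difference, and it gives no sizing figures for JPSE. Whether 0.27 is a slip in conversion or an unexplained input, it needs reconciling.

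**17 per group is just 34 divided by 2.** This is a natural reading. A reader might infer that two separate calculations, one by analysis of variance and one by t test, were run and happened to meet at 34. The document describes only one, and the fact that a t test also gives 17 per group is not evidence of a second. What remains is loose wording that calls an inflated number the number needed.

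**The gap is small.** It is: 2.65 points against 2.5 on an 11-point scale, and about three to five percentage points of power. That bears on the weight of the point, not on whether it is right.

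**Conclusion.** The point holds. The stated f = 0.27 is not the effect size given by the stated difference and SD, which is 0.25 at any correlation. At the correlation implied by the protocol's own N = 30 (about 0.5), the 2.5-point difference needs 34 evaluable pilots for 80% power. After the planned 10% loss from 34 enrolled, power is about 75% to 77%.

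The power figures assume equal groups, a two-sided 5% level, and either a correlation of about 0.5 with SD 2.5 at each time point, or 2.5 as the SD of the change. Over correlations of 0.3 to 0.6, power with 30 evaluable runs from 61% to 84%. The steps from f = 0.27 to 30 and from 30 to 34 are correct; the inconsistency is in the effect size fed into them. The paragraph should be corrected, but the shortfall is modest.

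**What to change.** Restate the Sample size paragraph from one calculation, in one of two ways:

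1. Keep 2.5 points and SD 2.5, use f = 0.25, state the assumed pre-post correlation and, if it is 0.5, report power of about 81% with all 34 evaluable and about 75–77% after 10% dropout.
2. Keep f = 0.27, state the correlation, and say that the trial is sized for 2.7 points at SD 2.5.

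In either case, reword the last sentence so that 17 per group is the dropout-inflated enrolment, not the number needed for 80% power.

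The cost is one reworded paragraph and, under the first option, a slightly lower stated power. No participants are added.

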## Statistical Analysis

A descriptive analysis will be performed for each of the variables. The normality of the variables will be evaluated using the Shapiro-Wilk test, which showed a normal distribution for all the variables and, thus, parametric tests will be appropriate. Data will be reported as mean # SD. The demographic and clinical variables of the groups at baseline will be compared using the chi-square test for categorical data and the independent-samples t-test for quantitative data. A 2-way repeated measure analysis of variance will be performed to analyse the interaction effects of time (at baseline and post-treatment) in the 2 intervention groups (experimental and control group). The independent and paired-samples t tests will be used for comparisons between and within groups, respectively. Furthermore, the effect size will be calculated through Cohen's d coefficient. A value above 0.8 will be considered high; 0.5 moderate; and lower than 0.2 will be considered low^41^. Significance level will be established at p < 0.05. Data analysis will be made with the statistic software SPSS version 26.0 (SPSS Inc., Chicago, IL, USA).

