- ***SD1 (ms):*** Sensitivity of short-term variability of the non-linear range of the HRV. It is considered an indicator of parasympathetic activity^32^.
- ***SD2 (ms)***: Long-term variability of the non-linear range of the HRV. It is a diameter from the Poincaré plot which indicates the degree of longitudinal dispersion. It is thought to reflect long-term changes in RR intervals and it is considered an inverse indicator of parasympathetic activity^32^.
- ***Stress Score (SS) (ms)***: It is an index described by Naranjo-Orellana et al.^32^ to facilitate the physiological interpretation of the Poincaré plot. It is expressed as the inverse of SD2 diameter multiplied by 1000.It is considered directly proportional to the sympathetic activity in the sinus node.
- ***Sympathetic/parasympathetic ratio (S/PS):*** It is also described by Naranjo-Orellana et al.^32^, S/PS is expressed as the quotient of SS and SD1. It is considered to reflect autonomic balance - that is, the relationship between sympathetic and parasympathetic activity.

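### The Protocol reports a Shapiro-Wilk result before the test is done, and its own definitions of SD2, SS and S/PS rule that result out as a claim of normality for every variable

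*Protocol*

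**What the plan says.** The Statistical Analysis section of the Protocol first plans a check: "The normality of the variables will be evaluated using the Shapiro-Wilk test". It then gives the outcome of that check and a conclusion from it: "Shapiro-Wilk test, which showed a normal distribution for all the variables and, thus, parametric tests will be appropriate". The methods that follow rest on this. "Data will be reported as mean # SD"; "A 2-way repeated measure analysis of variance will be performed to analyse the interaction effects of time"; "The independent and paired-samples t tests will be used for comparisons between and within groups, respectively". Effect sizes are Cohen's d. No transformation is named, and nothing limits the normality statement to a subset of variables.

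The section Outcome Measures of Heart Rate Variability lists, among others, rMSSD, LF, HF, LF/HF, SD1, SD2, the Stress Score (SS) and the S/PS ratio. SD2 is a variable in its own right ("Long-term variability of the non-linear range of the HRV"). For SS: "It is expressed as the inverse of SD2 diameter multiplied by 1000". For the ratio: "S/PS is expressed as the quotient of SS and SD1". Specific objective 6 asks for the effect of the programme on HRV. The Sample size section names NPRS and JPSE as the primary outcome.

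**The concern.** There are two faults in one sentence. First, a plan written ahead of the data cannot hold the result of a test on those data, yet that result is what justifies the choice of tests. Second, the result is claimed for all variables, and the list of variables includes one that is the reciprocal of another.

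What is at stake is the HRV part of the trial. If SS, S/PS and the power and ratio measures are right-skewed, raw means and SDs describe them poorly and raw-scale tests may lose power. The answer may also depend on whether the same quantity is tested as SD2 or as SS.

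**Working it through.** **Inputs.** From the Protocol: SS = 1000/SD2; S/PS = SS/SD1; 17 per group and two-sided alpha 0.05 (Sample size); groups of 14 and 17, together 31 (Intervention); two groups by two times (Statistical Analysis). Assumed, because the Protocol gives none: the spread of the HRV variables, the pre-post correlation rho, and the size of effect.

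The normality statement carries no figure to reproduce. The sample size does reproduce: for f = 0.27, noncentrality f²·N·2/(1 − rho) with rho = 0.5 gives N = 30 (power 0.815), and 30/0.9 = 33.3, rounded up to 34. That is why rho = 0.5 is used below.

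**Step 1: the definitions.** S/PS = SS/SD1 = 1000/(SD1 × SD2). A reciprocal stretches low values and compresses high ones. Take SD2 normal with an assumed coefficient of variation (CV) of 0.20. Two SDs below the mean, at the mean, and two SDs above it, SD2 is 0.6, 1.0 and 1.4 times its mean. SS is then 1/0.6 = 1.67, 1.00 and 1/1.4 = 0.71 times its central value. The upper distance is 0.67 and the lower 0.29, so SS is right-skewed. Conversely, if SS were normal, SD2 = 1000/SS would not be. SD2 and SS cannot both be normal, so SD2, SS and S/PS cannot all be.

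**Step 2: what Shapiro-Wilk would show.** Simulation, 4,000 runs per setting, with SD2 normal and truncated at 10% of its mean:

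| Assumed CV of SD2 | SS rejected, n = 17 | SD2 and SS both pass, n = 17 | SS rejected, n = 31 | SD2 and SS both pass, n = 31 |
|---|---|---|---|---|
| 0.15 | 24% | 74% | 40% | 57% |
| 0.20 | 36% | 62% | 61% | 37% |
| 0.30 | 63% | 34% | 89% | 9% |
| 0.40 | 79% | 19% | 97% | 2% |

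So the test can pass both variables in a sample of this size, even though in every row one of the two is certainly not normal. A pass does not show normality.

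**Step 3: power, post-treatment comparison only.** Let log Y be normal with SD s in each arm and shift one arm by s. On the log scale the standardised difference is 1 whatever s is, and 17 per arm give power 0.81. The t test on raw Y gives:

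| Assumed log SD | Raw-scale power |
|---|---|
| 0.2 to 0.3 | about 0.80 |
| 0.5 | 0.76 |
| 0.8 | 0.68 |
| 1.0 | about 0.61 |

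**Step 4: power, the planned interaction.** With two groups and two times, the interaction F is the square of the t test on change scores. On the log scale the variance of change is 2s²(1 − rho) = s² at rho = 0.5, so a shift of s again gives about 0.81. On the raw scale the result depends on direction:

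| Assumed log SD | Direction of effect | Raw-scale power |
|---|---|---|
| 0.3 | increase | about 0.82 |
| 0.5 | increase | 0.81 |
| 0.5 | decrease | about 0.61 |
| 0.8 | decrease | 0.45 |

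**Step 5: SD2 against SS.** log SS = log 1000 − log SD2. An increase in SD2 is therefore a decrease in SS of the same size and spread on the log scale. By Step 4, at log SD 0.5, one effect would have about 0.81 power tested as SD2 and about 0.61 tested as SS. For post-treatment values alone (log-normal SD2, CV 0.2 to 0.4, shift of 0.8 log SD, 17 per arm), the two raw t tests fall on opposite sides of 5% in 7% to 14% of trials. On the log scale they cannot disagree.

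The simulated powers in Steps 3 and 4 are good to about 0.01.

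**The case against.** The strongest reply has four parts.

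*The impossibility concerns exact normality, while t tests need only approximate normality.* This stands in part. At small spread the raw scale costs almost nothing (0.80 against 0.81), and a small-sample Shapiro-Wilk test may reject nothing. What falls is the use of such a pass as proof that parametric tests suit every variable.

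*False positives are not inflated.* This stands. With 14 against 17 and no effect, raw-scale type I error stays at 0.04 to 0.05. The issue is power, description and consistency.

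*Scale and fallback methods belong in a statistical analysis plan.* This stands for a missing fallback, which is not raised here. It does not cover a result stated in the Protocol and used as the reason for the tests. That the analysis is on the raw scale is itself inferred, from the reporting of means and SDs and the absence of any transformation.

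*The wording may be pasted.* This is quite possible. A reader might infer that the data had been seen and the tests chosen afterwards, all the more because the Intervention section describes the programme in the past tense with groups of 14 and 17. The Protocol does not establish that. Stray past tense also appears in the sections on myoelectric activity and electromassage, and the tests themselves are named outright.

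A reader might also infer that the primary analysis is unsound. Nothing here shows that. The eligibility minimum of 3 on the NPRS restricts baseline scores only, and no loss was demonstrated for NPRS or JPSE.

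**Conclusion.** The point holds in a limited form. The Protocol states a test result it cannot yet have, and as a claim about distributions that result contradicts its own definitions of SD2, SS and S/PS. Both follow from the text and need no assumption.

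The size does need assumptions: log-normal HRV indices, a shift of one log SD, 17 per arm and rho = 0.5. Under them, raw-scale power for the planned interaction runs from about 0.82 to 0.45, against about 0.81 on the log scale. The loss may be nil or substantial, and the Protocol offers no HRV spread to narrow it. The consequence is confined to the HRV outcomes. The sample size and the primary analysis are untouched. Severity is minor.

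**What to change.** 1. Delete the reported Shapiro-Wilk result and the inference drawn from it.
2. State in advance that rMSSD, LF, HF, LF/HF, SD1, SD2, SS and S/PS are analysed on the log scale and reported as geometric mean ratios. Because log SS is a constant minus log SD2, one test serves both. pNN50 is left out of this list because it is a percentage that can be zero; its scale should be named separately.
3. Judge the residuals of the fitted model instead of testing the raw variables for normality.

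The cost is a few lines of text and slightly different output. The downside is that HRV effects are read as ratios, not differences. No participants are added.

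A separate option is to adjust the post-treatment comparison for the baseline value already collected. At rho = 0.5 the error variance is 1 − 0.5² = 0.75 of the single-time variance, against 2(1 − 0.5) = 1.0 for change scores. That is a gain in precision at no cost in data. It is not a remedy for non-normality and should be proposed on its own merits, since the sample size was set on the group-by-time interaction.

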## Participants

Convenience sampling will be followed. The inclusion criteria will be: (i) fighter pilots (male and female) who, at the time of the assessment, are an instructor or student attached to the 23rd Wing of the Talavera Air Base, Air Force (FAE), Badajoz; (ii) fighter pilots diagnosed with flight-related neck pain according to the International Classification proposed by a NATO expert panel4; (iii) fighter pilots diagnosed with flight-related neck pain according to the International Classification proposed by a NATO expert panel; (iv) fighter pilots diagnosed with flight-related neck pain according to the International Classification proposed by a NATO expert panel5; a minimum perceived pain score of 3/10 on the Numerical Pain Rating Scale (NPRS) on the early morning assessment within 48 hours of the last flight; (iv) scores of ≥5 points on the Neck Disability Index (NDI), and a cervical positioning error of ≥4.5°^19^. Exclusion criteria shall be: (i) Personal Psychological Apprehension Scale (PPAS) score greater than 37.5^20^; (ii) contraindication to electrical stimulation; (iii) having received physiotherapy or any other routine medical care six weeks prior to data collection; (iv) any regular use of medications known to affect autonomic nervous system (ANS) function or pain perception, including opioids, antidepressants, benzodiazepines, anti-inflammatory drugs and beta-blockers, two weeks prior to participation in this study; and (v) being involved in ongoing medico-legal disputes.

- - 1. Numeric Pain Rating Scale

Numeric Pain Rating Scale (NPRS) is a 11-point numeric rating scale, where 0 denotes “no pain” and 10 denotes “the maximum bearable pain”. The minimum clinically important difference (MCID) for this tool have been established at 1.3 points and the minimum detectable change (MDC) at 2.1 points^9^, in individuals with neck pain. The NPRS is a valid scale with moderate test-retest reliability in this population (ICC: 0.76, 95% CI 0.51 to 0.87)^9,21^.

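### The unadjusted time-by-group ANOVA is valid but less precise than ANCOVA, and the paired within-arm t tests can turn significant through regression to the mean alone

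*Protocol*

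**What the plan says.** The Statistical Analysis section of the Protocol sets out the main model as follows: "A 2-way repeated measure analysis of variance will be performed to analyse the interaction effects of time". The model has two time points, before and after treatment, and two arms. No covariate is named. Baseline values enter only as the first of the two time points and in a comparison of the groups at baseline.

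The section then adds: "The independent and paired-samples t tests will be used for comparisons between and within groups, respectively". One threshold covers everything: "Significance level will be established at p < 0.05". The t tests are not called descriptive, are not made conditional on the interaction, and are not ranked below it.

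Two other sections bear on this:
- **Participants.** Entry requires "a minimum perceived pain score of 3/10 on the Numerical Pain Rating Scale (NPRS"), an NDI of at least 5 and a cervical positioning error of at least 4.5 degrees. The same section gives a test-retest ICC of 0.76 for the NPRS.
- **Sample size.** NPRS is named as a primary outcome. The calculation uses "Assuming an effect size (F-test) of 0.27 for ANOVA: repeated measures, within-between interaction groups differences", and a difference of 2.5 NPRS points with an SD of 2.5.

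**The concern.** There are two separate issues.

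**Precision.** A 2x2 time-by-group interaction compares raw change between arms, which fixes the slope of post on baseline at 1. The independent t test on the post value fixes it at 0. The real slope normally lies between, and ANCOVA estimates it. In a trial of about 30 pilots any avoidable variance matters.

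**Within-arm tests.** A paired t test in one arm is not a randomised comparison. Pilots are admitted because their scores are high enough, so scores are expected to fall on re-measurement even without treatment. A significant fall in the experimental arm, perhaps next to a non-significant one in the control arm, could then be reported as benefit while the randomised comparison shows nothing.

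**Working it through.** **Inputs from the Protocol.** Difference 2.5 NPRS points; SD 2.5; f = 0.27; two-sided alpha 0.05; power 80%; total of 30 before inflation, so 15 per arm; NPRS entry threshold 3; NPRS test-retest ICC 0.76.

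**Assumed, because not stated.** Baseline-post correlation rho (0.3 to 0.76); underlying NPRS mean before selection (3 to 6); normal scores; 2.5 taken as the SD before selection; the qualifying score is also the analysed baseline.

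**1. The plan's own figure.** For the interaction, lambda = f² × N × 2 / (1 − rho), with 1 and N − 2 degrees of freedom. At rho = 0.5 and N = 30, lambda = 0.0729 × 30 × 2 / 0.5 = 8.75 and power is 0.815. The smallest balanced N reaching 80% is 30, so the stated total reproduces. It does so only near rho 0.5: rho 0.3 needs 40 and rho 0.7 needs 20. Here f = 0.27 means a difference in change of 4 × 0.27 = 1.08 SD, or 2.7 points. The stated 2.5 points is 1 SD.

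**2. Precision with an unselected baseline.** In units of SD²:
- raw change (the interaction): 2(1 − rho)
- post value only: 1
- ANCOVA: 1 − rho²

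Change relative to ANCOVA is 2/(1 + rho), and post-only relative to ANCOVA is 1/(1 − rho²). Both exceed 1 for every rho between 0 and 1. Non-central t power for 2.5 points, SD 2.5, 15 per arm:

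| rho | variance ratio, change/ANCOVA | change (interaction) | post-only t test | ANCOVA |
|---|---|---|---|---|
| 0.3 | 1.54 | 0.608 | 0.753 | 0.790 |
| 0.5 | 1.33 | 0.753 | 0.753 | 0.862 |
| 0.7 | 1.18 | 0.927 | 0.753 | 0.959 |

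**3. Precision with baseline cut off at NPRS 3.** Selection narrows the baseline. The ANCOVA residual variance stays at SD²(1 − rho²), while the change variance becomes SD²(1 − rho²) + (1 − rho)² × Var(selected baseline). For an underlying mean of 4, the selected baseline SD is about 1.7 (variance about 2.9):
- rho 0.5: 4.69 + 0.25 × 2.9 = 5.4 against 4.69, ratio 1.15
- rho 0.76: 2.64 + 0.058 × 2.9 = 2.81 against 2.64, ratio 1.06

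Simulated power (20,000 trials per row, 2.5 points, 15 per arm):

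| underlying mean | rho | change (interaction) | ANCOVA |
|---|---|---|---|
| 3 | 0.5 | 0.82 | 0.85 |
| 4 | 0.5 | 0.81 | 0.85 |
| 5 | 0.5 | 0.80 | 0.85 |
| 6 | 0.5 | 0.78 | 0.85 |
| 3 to 6 | 0.76 | 0.97 to 0.98 | 0.98 |

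**4. Paired test with no effect.** The expected fall is (1 − rho) × (E[X given X ≥ 3] − mean). For mean 3 and rho 0.5 this is 0.5 × (4.99 − 3) = 1.00 points. The same simulations without an effect, 15 in the arm, give the share of trials in which the paired test declares improvement (nominal 2.5%):

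| underlying mean | expected fall, rho 0.5 / 0.76 | false improvement, rho 0.5 / 0.76 |
|---|---|---|
| 3 | 1.00 / 0.48 | 35% / 18% |
| 4 | 0.70 / 0.34 | 19% / 10% |
| 5 | 0.46 / 0.22 | 10% / 7% |
| 6 | 0.27 / 0.13 | 6% / 5% |

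In the same runs the interaction and the between-group t test rejected in about 5% of trials, as they should.

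**The case against.** The case for leaving the plan alone has four parts.

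- **The between-group tests are sound.** Regression to the mean acts on both arms alike and cancels in the randomised comparison; both tests hold their 5% level. This stands. A reader might infer that selection on baseline biases the planned efficacy test. It does not: the first issue is lost power only.
- **The main test is implied.** The trial is sized on the interaction, and the analysis section lists it first. This largely stands. A reader might infer that the protocol lets a paired test decide efficacy. Nothing says so, and a statistical analysis plan could settle the ranking. But the protocol does commit to paired tests at 0.05 as comparisons in their own right, without limiting their role.
- **The power gain is easily overstated.** The 75% to 86% contrast assumes an unselected baseline, whereas the regression argument assumes a selected one. Under selection the gain at rho 0.5 is a few percentage points, and if the ICC of 0.76 approximates the four-week correlation (itself an assumption) it is about one point or less. This stands. A reader might infer from the 75% that the trial falls short of its 80% target, but that depends on an unstated rho and an unselected baseline.
- **The paired-test rates rest on assumptions.** Pilots with diagnosed pain, assessed within 48 hours of flight, may have a higher underlying mean, and at 5 to 6 the rate is only 5% to 10%. A normal distribution with mean 3 and SD 2.5 puts about 11% of scores below zero. After selection the baseline SD is no longer 2.5. A baseline reading separate from the qualifying one would reduce the fall. All of this limits the size, not the direction.

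**Conclusion.** The point holds as an improvement to the analysis wording, not as a flaw that invalidates the trial. The planned interaction and between-group t test are valid but less precise than ANCOVA. At rho 0.5 the power difference is 75% against 86% with an unselected baseline, and about 80 to 81% against 84 to 86% with entry cut off at NPRS 3 (underlying means 4 to 5). At rho 0.76 there is almost no gain.

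The paired tests should not carry inference. Without any effect they indicate improvement in roughly 5% to 35% of trials instead of 2.5%, across assumed underlying means of 6 down to 3 and rho of 0.76 to 0.5, provided the qualifying score is the analysed baseline. Confidence is high on direction. It is limited on size, because the protocol states neither rho nor the expected baseline mean.

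**What to change.** In the Statistical Analysis section of the Protocol, make the single efficacy test for each outcome an ANCOVA of the post-treatment value on arm, with that outcome's baseline value as covariate, reported as the adjusted mean difference with 95% CI. Remove the independent and paired t tests as inference, and present within-arm change descriptively only, without p-values.

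The cost is a reworded paragraph, one degree of freedom and the loss of within-arm p-values. Baseline is already collected, and the named software fits the model. The sample size need not change on this account.
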